### Interventions

#### Web-based relapse prevention program: e-SMARPP

The website of e-SMARPP is comprised of five modules: (1) cognitive behavioral relapse prevention sessions (watching videos, submitting exercises and a weekly dairy on the website), (2) self-monitoring, calendar that displays drug use status by color, (3) information, downloadable PDF and website links to drug addiction support services, (4) user guide, how to use the system, frequently asked questions and a contact form to researchers and (5) assessment, which are web-based questionnaires for baseline and three follow-up assessments.

The main intervention modules are the relapse prevention program sessions and self-monitoring. Content for the videos and exercises of the relapse prevention program are taken from the SMARPP workbook and can be adapted to any type of drug. Each session has three videos, two exercises and a weekly diary activity (Table 1). Videos are made in a YouTube format and embedded in each session (See Fig. 2). Videos are online, but are unlisted videos and restricted to people who have the link to the video, so only participants in the intervention group and researchers can view them. Narration and subtitles help users understand the content. Exercises are related to the video content and users will be expected to complete these after watching the video. Users will write and submit their own answers through an Internet text form (See Fig. 3). In addition, users are expected to write down in the weekly diary their condition from the last week, current goals, and how they will plan to spend time over the next week. Writing in the diary is also done on the Internet through the system. After submitting the exercise and the weekly diary, users receive tailored feedback comments from qualified health care professionals (registered nurse and medical doctor) who are trained to support patients with substance use disorders (mainly AT). Feedback comments are based on motivational interviewing skills to enhance user motivation and to provide individual support.

**Table 1 Tab1:** Content for relapse prevention session of e-SMARPP

1. What is drug dependence?	
Video	➢ Mental and physical consequences caused by drug use (11′ 02″)
	➢ Changes in the brain (11′ 39″)
	➢ How to stop a drug craving (7′ 43″)
Exercise	■ Think about your pros and cons for drug use and quitting drugs.
	■ Define your drug use situation: when, where, who, why, what and emotion.
2. Triggers of drug use	
Video	➢ Process of craving and drug use (5′ 27″)
	➢ Various internal and external triggers of drug craving (11′ 00″)
	➢ Anchors keeping you from drug use (5′ 01″)
Exercise	■ Define your internal and external triggers.
	■ Who and what are your anchors?
3. Recovery process; “Just for today”	
Video	➢ Process and stage of recovery (12′ 38″)
	➢ Safe lifestyle and signs of relapse (10′ 19″)
	➢ How to plan a safe daily life (9′ 27″)
Exercise	■ Think of your signs of relapse and barriers to recovery.
	■ Plan a safe daily life schedule without drugs.
4. Features of dependence symptoms	
Video	➢ Typical features of dependence (9′ 05″)
	➢ Typical thoughts and behaviors when people fall for drugs (12′ 32″)
	➢ Justification for relapse (9′ 21″)
Exercise	■ Think of your patterns of thinking and behavior during drug use
	■ Think of your possible justification for relapse
5. Supporters for recovery	
Video	➢ Typical internal triggers: “HALT” (hungry, angry, lonely and tired) (10′ 05″)
	➢ To trust and be honest to yourself and others (5′ 41″)
	➢ Support from peers and professionals (13′ 39″)
Exercise	■ Think of ways to handle internal triggers.
	■ Think of your supporters. Who? How to find?
6. No need to be strong, be smart and practiced	
Video	➢ Tips for recovery (6′ 04″)
	➢ Review of skills to handle triggers and relapse (12′ 21″)
	➢ To accept the way you are, messages from peers (4′ 32″)
Exercise	■ Think of crisis plans when you relapse into drug use.
	■ Think of your future when you recover from drug addiction.

Each session also includes a weekly diary activity

Parentheses indicate minutes and seconds of each video

**Fig. 2 Fig2:**
[figure not shown]
Screenshot of video

**Fig. 3 Fig3:**
[figure not shown]
Screenshot of exercise

The self-monitoring is done in a calendar format, using a plug-in from Moodle, to provide a function similar to the self-monitoring process utilized in SMARPP. Users click on a date in the calendar and select one of three colors (red, yellow or blue), then that color subsequently displays on the date (See Fig. 4). The colors represent the user’s drug use: red reflecting abuse of the primary drug; yellow reflecting secondary abuse of other drugs and alcohol use; and blue indicating no drug and alcohol use. Instructions and a legend for colors are not displayed on the Web page to avoid concerns about confidentiality. Participants are provided an explanation about the colors and how to use the calendar at the time of study enrollment. This calendar is intended to record only presence or absence of drug use without quantity and frequency a day because primary abused drug will vary and the total quantity will not be able to be adequately compared. We prioritized a user-friendly system without many options for drug names and units. An optional memo function is provided for personal user use that records detailed conditions (drug form, quantity and frequency, triggers, etc.).

**Fig. 4 Fig4:**
[figure not shown]
Screenshot of self-monitoring calendar

A self-monitoring calendar is used as a measure to assess drug use for a period of 28-days before the baseline and for follow-up assessments like the Timeline Followback (TLFB) method [28, 29]. Web-based versions of the TLFB methods have been developed and adapted to various substances with good reliability and validity [30–32] and have been used in some intervention studies [11, 19–21].

e-SMARPP is equipped with some automated functions for participants, including progress tracking and a notification e-mail when they receive feedback. In the notification e-mails, a related webpage link is shown and users can access the webpage directly. For example, users can view the feedback comment webpage directly after they click the link in the notification e-mail. Additionally, for researchers who registered on e-SMARPP, a notification e-mail will be sent when participants submit an exercise, diary and questionnaire.

#### Intervention group

Participants who are assigned to the intervention group are provided access to the complete contents of e-SMARPP, including six sessions for cognitive behavioral relapse prevention and web-based self-monitoring. They are expected to complete each session over a week in sequence order by each deadline (each Sunday). For an 8-week intervention period, they are expected to complete a total six sessions, but they have a 2-week grace period and are allowed to progress at their own pace. If they do not complete a session, the session will be carried over to the next week. Participants will be expected to record their daily situation of drug use on the web-based self-monitoring calendar by each deadline (each Sunday). If they do not go through an expected session and/or self-monitoring by each deadline, a researcher will send an e-mail reminder on the next day (Monday).

Participants continue to receive outpatient treatment as usual, including medication, face-to-face group or individual psychosocial treatment programs and counseling by psychologists and/or social workers. Provided treatment depends on individual condition. Even if participants stop receiving outpatient treatment or change their primary doctor and hospital, the web-based intervention will not be cancelled.

#### Control group

Participants who are assigned to the control group are provided access to a part of the contents of e-SMARPP, including the web-based self-monitoring and information content. Control group participants have no access to the cognitive behavioral relapse prevention sessions. Similar to the intervention group, they are expected to record their daily situation of drug use on the web-based self-monitoring calendar by each deadline (each Sunday). If they do not go through the self-monitoring by each deadline, a researcher will send an e-mail reminder on the next day (Monday). They will continue to receive outpatient treatment as usual similar to the intervention group. After the study period, cognitive behavioral relapse prevention sessions will be provided if requested.

### Measures

#### Data collection procedure

Table 2 shows an assessment schedule for this study. Data collection will be conducted through web-based self-reported questionnaires on the e-SMARPP website at baseline (T1) and follow-up assessments at 2 (T2), 5 (T3) and 8 (T4) month after the randomization. Participants will be informed about the follow-up assessments via e-mail and asked to complete the questionnaire within 1 week. After 1 week, an additional reminder e-mail will be sent to non-respondents. If a participant’s e-mail address changes and an e-mail is not received, a postcard will be sent as an extra reminder. Participants will receive a prepaid card for 1000 yen as a reward for baseline and each follow-up assessment that they complete.

**Table 2 Tab2:** Assessment schedule of primary and secondary outcomes

Outcome		Measurement	Baseline (T1)	2-month follow-up (T2)	5-month follow-up (T3)	8-month follow-up (T4)
Primary outcome						
1	Relapse risk	SRRS	x	x	x	x
2	Longest consecutive duration of abstinence	Longest duration of consecutive abstinent days during the intervention #		x		
Secondary outcome						
1	Motivation to change	SOCRATES	x	x	x	x
2	Self-efficacy for handling drug use and craving	Self-efficacy Scale for Drug Dependence	x	x	x	x
3	Percentages of abstinent days	Abstinent days in the past 28 or 56 days #	x	x	x	x
4	Differences in change of abstinent days	Summed abstinent days in the past 28 days #	x	x	x	x
5	Health related quality of life	WHOQOL26	x	x	x	x
6	Sense of coherence	3-item sense of coherence scale	x	x	x	x
7	Cost of alcohol and drug	Self-reported cost of drugs or alcohol in the last month (yen)	x	x	x	x
8	Treatment retention	Yes or no	x	x	x	x
9	Self-help group use	Yes or no	x	x	x	x
10	Psychiatric medical cost	Self-reported medical use in the past six months	x			x
Feasibility and usability outcome						
1	Program completion	Number of completed weeks		x		
2	Satisfaction	CSQ-8		x		
3	Usability and usefulness	Original questionnaire		x		

*SRRS* Stimulant Relapse Risk Scale, *SOCRATES-8D* Stage of Change Readiness and Treatment Eagerness Scale-8 version for drug use, CSQ-8, 8-item Client Satisfaction Questionnaire

#: Self-reported drug use or abstinence assessed by web-based self-monitoring calendar or the Timeline Follow-back method

#### Primary outcome

The primary outcomes will be relapse risk, assessed using the Stimulant Relapse Risk Scale (SRRS) [33, 34], and the longest duration of consecutive abstinence (days). SRRS was developed to measure multidimensional relapse risk and consists of 35 items measured on a 3-point Likert scale. The SRRS has five subscales: anxiety and intention to use drug (AI), emotionality problems (EP), compulsivity for drug use (CD), positive expectancies and lack of control over drug (PL), and lack of negative expectancy for drug use (NE) [33]. All items ask about a drug-related situation in the past 1 week. Examples of the items are “I am anxious about reusing the drug” (AI), “I cannot control my feeling” (EP), “I want to obtain the drug even by working illegally” (CD), “If I use the drug, I would feel invigorated” (PL), and “If I use the drug, it would badly influence my job” (NE, inversed item). Higher average scores for total and subscale items indicate higher relapse risk. Its reliability and validity was confirmed among stimulant drug users in Japan [33].

We will add another primary outcome, the longest duration of consecutive abstinence (days), according to previous studies [19–21]. This is because the cut-off point of the SRRS has not been confirmed and interpretation of the score is difficult. Additionally, the SRRS was developed and is only used in Japan, and as such, a more objective outcome measure is needed. The longest duration of consecutive abstinence from the primary abused drug during intervention (56 days) will be counted, using the self-monitoring calendar and the TLFB method.

We hypothesize that both of the two primary outcomes will differ significantly between groups.

#### Secondary outcome

The secondary outcomes (Table 2) will be the following ten measures.

##### Motivation to change

Motivation to change will be measured with the Stage of Change Readiness and Treatment Eagerness Scale-8 version for Drug Use (SOCRATES-8D) [35, 36]. The SOCRATES-8D consists of 19 items assessed on a 5-point Likert scale and three subscales: Recognition, Ambivalence, and Taking Steps. Examples of the items are “I really want to make changes in my use of drugs” (Recognition), “Sometimes I wonder if I am an addict” (Ambivalence) and “I have already started making some changes in my use of drugs” (Taking Step). Higher scores indicate higher motivation to change. Positive correlations have been reported between high scores and the development of readiness for treatment [37] and engagement in treatment [38]. Reliability and validity of the Japanese version of the SOCRATES-8D has been confirmed [35, 39]. However, a different factor structure (two-factor structure) was observed in the previous study [35], so we will use only the total score in this study.

##### Self-efficacy

Confidence (i.e., self-efficacy) in handling drug use and craving is measured with the Self-efficacy Scale for Drug Dependence (SSDD) [40]. The SSDD has two domains: general self-efficacy (GE) and self-efficacy in specific situations (SS). The GE domain consists of five items assessed on a 5-point Likert scale from 1 (not confident) to 5 (confident). Examples of GE items include, “I can seek help when I have a problem”. The SS domain consists of 11 items assessed on a 7-point Likert scale from 1 (not at all confident) to 7 (absolutely confident). Examples of an SS item includes, “I can handle a drug craving when I am depressed and anxious”. Higher GE and SS scores mean more confidence in handling a drug craving.

##### Abstinence

Abstinence from the primary abused drug will be measured using the following three methods. First, percentages of abstinent days from the primary abused drug in the past 28 or 56 days at each assessment point will be compared. Next, differences in change of abstinent days from the primary abused drug in the past 28 days between baseline (T1) and follow-up (T2, T3 and T4) will be assessed. Finally, the longest consecutive abstinent days during the intervention period will be compared. Abstinent days will be summed using self-monitoring and the TLFB method.

##### Quality of life

Health related quality of life measured with WHO/QOL-26 [41], which consist of 26 items measured on a 5-point Likert scale. There are two items which asks about an individual’s overall perception of quality of life (QOL) and their health. The remaining 24 items are divided into four domains: physical domain, psychological domain, social relationships and environment. All items ask about respondents’ life in the last 4 weeks. Higher scores indicate higher QOL.

##### Sense of coherence

Sense of coherence (SOC) is considered to be an individual’s personality as a fundamental source of coping in stressful events [42]. The SOC of people with substance use disorder has been considered lower than that of healthy people [43]. Among people with mental health problems and substance use disorders, previous studies have revealed that high SOC is associated with a better ability to cope with stressful life situations and improved life satisfaction [43, 44] and high SOC is one of the predictors of treatment success: treatment retention and drug abstinence [45]. We will use the University of Tokyo Health Sociology version of the SOC3 scale (SOC-3-UTHS) [46, 47], which consists of three items measured on a 7-point Likert scale. A higher score indicates a higher SOC.

##### Treatment retention and alternative treatment use

We also will assess participants’ retention of outpatient treatment and use of self-help group such as narcotics anonymous.

##### Cost of substance use and treatment use

Total cost of alcohol and drug use in the past month will be asked separately. In Japan, methamphetamine is more expensive than other drugs (above 10,000 yen for use of methamphetamine several times). New psychoactive substances (NPS) are relatively cheap (about 2000 to 5000 yen for one package).

Cost of psychiatric treatment use in the past 6 months will also be assessed. We will ask about frequency and period of psychiatry hospitalization and outpatient treatment, frequency of use of emergency room, total cost of prescription drugs, frequency and period of specialized outpatient treatment for drug addiction, the participant’s income and amount of time required to receive one outpatient treatment including travel time. We will calculate total psychiatric medical cost using the annual report of medical costs by diseases and treatment [48].

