## Methods

### Trial design

Figure 1 shows the design of this study and participant flow. This study is a two-arm (allocation ratio is one to one), parallel-group, non-blinded and multicenter randomized controlled trial. Eligible participants are asked to complete the baseline assessment and are randomly allocated to either the intervention group or the control group. All participants in both groups will be provided a login/password with instructions about how to access the website and use e-SMARPP during the study. The participants in the intervention group can access the complete contents of e-SMARPP, while the control group can access a part of it: self-monitoring. Each individual access account is tied to either group, and as such participants can use e-SMARPP content included in their group only. Web-based follow-up assessments are conducted at 8, 20, 32 weeks after the baseline assessment.

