### Randomization and blinding

Staff of recruiting institutions will recruit outpatients who meet inclusion criteria. Eligible participants will be informed that they will be allocated to either of the two groups. After baseline assessment, they will be randomly assigned to either of the two groups using the method of permuted block, with random block size of four, and they will be informed their assigned group by the first author (AT). Randomization will be stratified by institution. The computer-generated allocation list was made by an independent researcher (YM) and concealed to other researchers and participants until the time of assignment. The enrollment is conducted by the first author (AT) and the intervention starts immediately. Researchers and staff who work for recruiting institutions will be blinded. In addition, an independent researcher (YM) who will not analyze data will download data from the e-SMARPP database and an independent research staff person will mask the group variable before analysis, then researchers (AT and [name]) will analyze data that is blinded to the group variable.

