#### Cost effectiveness analysis

Health economic evaluation will be undertaken using data generated within the present trial, to provide information on the ‘value’ of allocating resources to the e-SMARPP (plus usual care) strategy over self-monitoring (plus usual care). The research question regarding the economic evaluation is, ‘Is e-SMARPP potentially a cost-effective means of helping abuse drug users to increase abstinent days? Specifically, we will employ a cost-effectiveness analysis (CEA) framework, and the results of analysis will be summarized as an incremental cost-effectiveness ratio (ICER). A within-trial analysis will evaluate cost-effectiveness from a patient and institutional perspective. Sensitivity analysis will be undertaken for parameter uncertainty of benefits measures and assumptions to calculate average costs. Subgroup analysis will be of great interest to make policy recommendations for a more targeted approach. Subgroups categorized by variables set in the main trail analysis, e.g., types of abuse drug primarily used, will be adopted for this subgroup analysis in an economic evaluation.

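### Psychiatric treatment use is asked only at baseline and T4 with six-month recall, so about 74% to 100% of the 8-week intervention goes uncosted in the cost-effectiveness analysis

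*Protocol article*

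**What the plan says.** **Recall period.** The section on cost of substance use and treatment use states: "Cost of psychiatric treatment use in the past 6 months will also be assessed". The items cover hospitalization, outpatient and specialized addiction treatment, emergency room use and prescription costs. Table 2 repeats the recall period for secondary outcome 10: "Self-reported medical use in the past six months". It marks that outcome at baseline (T1) and T4 only; T2 and T3 are blank.

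**Timing of T4.** The trial design section gives weeks: "Web-based follow-up assessments are conducted at 8, 20, 32 weeks after the baseline assessment". The data collection section gives months: "follow-up assessments at 2 (T2), 5 (T3) and 8 (T4) month after the randomization".

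**Intervention period.** The randomization section says that after enrolment "the intervention starts immediately". The intervention group section gives the length: "For an 8-week intervention period, they are expected to complete a total six sessions". The primary outcome section gives the same length in days: "The longest duration of consecutive abstinence from the primary abused drug during intervention (56 days) will be counted".

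**Economic analysis.** The cost-effectiveness section says: "A within-trial analysis will evaluate cost-effectiveness from a patient and institutional perspective". The effect is abstinent days and the summary is an incremental cost-effectiveness ratio (ICER). Each strategy is defined as including usual care. The section names neither a period for costs nor a period for effects.

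**The concern.** A within-trial ICER needs resource use from randomization to the end of follow-up. Here the two reports leave a hole: the baseline report ends at randomization, and the T4 report does not reach back that far. The hole falls on the weeks in which the programme is delivered, when an adjunct programme could plausibly change use of usual care. Because usual care is part of both strategies, its cost belongs in the comparison.

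Any saving or extra use in those weeks, in either arm, cannot enter the incremental cost. An analysis plan written later cannot recover answers to a question that was never asked. The article itself fixes both the recall length and the assessment points, so this is not a detail left to a fuller document.

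**Working it through.** The plan states no figure for cost coverage, so there is none to reproduce. The check is interval arithmetic on its own schedule.

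**Inputs**
- Recall at T4: 6 months (cost section; Table 2). Taken as 6 calendar months, 6 × 365.25/12 = 182.6 days, or as 26 weeks = 182 days.
- T4: 32 weeks = 224 days (trial design), or 8 calendar months = 243.5 days (data collection).
- Intervention: days 0 to 56. Baseline assessment, randomization and start of intervention are treated as the same day.

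**Formulas**
- First day covered = T4 day − recall length.
- Share of intervention uncosted = min(56, first day covered) / 56.
- Share of follow-up uncosted = first day covered / T4 day.

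**Results**

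| T4 | Recall | First day covered | Intervention uncosted | Follow-up uncosted |
|---|---|---|---|---|
| 224 days | 182.6 days | 224 − 182.6 = 41.4 | 41.4/56 = 73.9% | 41.4/224 = 18.5% |
| 224 days | 182 days | 224 − 182 = 42 | 42/56 = 75.0% | 42/224 = 18.8% |
| 243.5 days | 182.6 days | 243.5 − 182.6 = 60.9 | 56/56 = 100% | 60.9/243.5 = 25.0% |
| 243.5 days | 182 days | 243.5 − 182 = 61.5 | 56/56 = 100% | 61.5/243.5 = 25.3% |

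Reading 6 months as 180 days gives 78.6% of the intervention with T4 at 32 weeks, and again 100% with T4 at 8 months. The result depends little on how a month is counted; it depends mainly on which timing of T4 applies.

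**Effect side.** Abstinent days are scheduled over the past 28 or 56 days at each assessment. Against a 182.6-day cost window these are 28/182.6 = 15.3% and 56/182.6 = 30.7%, so no scheduled abstinence window equals the cost window. The 56-day intervention window overlaps the cost window by 56 − 41.4 = 14.6 days at most, and by 0 days with T4 at 8 months.

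**Can abstinent days cover the whole follow-up?** With 56-day windows ending at weeks 8, 20 and 32, the covered weeks are 0–8, 12–20 and 24–32. Weeks 8–12 and 20–24 are unmeasured. With 28-day windows the covered weeks are 4–8, 16–20 and 28–32, so the gaps are larger.

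**The case against.** **Other cost data exist for the intervention period.** This stands, and it limits the point. A reader might infer that all costs during the intervention are lost; the article does not support that. Drug and alcohol spending is asked for the last month at every assessment, so T2 covers roughly the second half of the intervention. Programme delivery cost does not depend on the T4 recall item. Hospitalization during the intervention is collected from the primary doctor, and treatment retention is recorded as yes or no at T2. However, the hospitalization data are adverse event information and are not described as a cost source. Neither source gives outpatient frequency, emergency use or prescription cost.

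**The effect window is not stated.** This also stands. A reader might infer that the ICER will set abstinence gained during the intervention against costs that exclude that period. The cost-effectiveness section does not say so, and an analyst could pair abstinence at T4 with the T4 cost window. What remains is narrower: whichever scheduled abstinence window is chosen, it is not the six-month cost window.

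**Equal six-month windows at T1 and T4 allow a like-for-like comparison.** With T4 at 8 calendar months, the window is close to the post-intervention period. That is a sensible reason for secondary outcome 10 taken alone. It does not give a within-trial ICER the missing weeks.

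**Recall is the same in both arms, so the horizon is truncated rather than biased.** Partly right. Bias in incremental cost arises only if the arms differ in treatment use during the uncovered weeks, and nothing in the article shows that they do.

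**Conclusion.** The gap is real, but it is confined to psychiatric treatment use. As scheduled, such use is not costed for about 74–75% of the 8-week intervention if T4 is at 32 weeks and for all of it if T4 is at 8 calendar months. That is about 18–25% of follow-up. These figures assume that recall runs a full six months back from the day of the T4 assessment, and that baseline and randomization coincide.

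The documents do not support saying that the ICER is biased in a known direction, or that it must be biased at all. They support saying that a difference between arms in those weeks would go unseen. The mismatch of cost and effect windows is an inference from the assessment schedule, not a stated feature of the economic analysis.

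The primary outcomes and the rule for declaring the intervention effective are untouched. The change is still worth making, because the lost data cannot be recovered by analysis and the repair is cheap.

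**What to change.** - **T2.** Add the same medical-use items to the existing web questionnaire, with recall since randomization.
- **T4.** Anchor the item to the period since T2. That is 32 − 8 = 24 weeks, or 8 − 2 = 6 months, so comparability with the six-month baseline item is nearly kept.
- **Participants already past T2.** Add a separate T4 question on the period from randomization to T2.
- **Costs.** Sum from randomization to T4. Uncovered intervention days then fall from 41–56 to 0.
- **Effects.** State the effect window of the ICER. One option is to pair abstinence over the 56 intervention days with costs to T2. The other is to say that abstinent days over the full follow-up cover only the scheduled windows, unless calendar recording or Timeline Followback recall is extended. Defining abstinent days over the full 0–32 weeks is not possible with the scheduled data.

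**Cost.** A few more web items at T2, with ethics notification, and longer recall for those past T2. Extending calendar or Timeline Followback recall, if chosen, would add participant burden.
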